### **Sample size Determination**

The sample size will be used to test the following statistical hypothesis as stipulated earlier:

**Hypothesis:** The three therapies differ by clinically relevant amounts

**Alternative Hypothesis:** The three therapies do not differ by clinically relevant amounts

A cure rate of 85% to 95% was used in the sample size calculation, where 85% represents the worst-case scenario and 95% the best outcome. The difference of these two proportions gives the size of the treatment effect sought in the randomized clinical trials.

This means that we are dealing with a dichotomous variable where the patients will be categorized as cured or not cured. A power of 90% and 5% level of significance are also required. The calculated sample size was adjusted for attrition and other covariates such as HIV/AIDS which was observed to be high in some of the participating countries.

Allocation adopted – uniform and equal allocation where  $\lambda = n_t/n_c = 1$

The sample size  $n = r * n_t$  [r is the number of active groups] which is calculated as follows:-

$$n_t [\text{per arm}] = k * [(p_1(1-p_1) + p_2(1-p_2))/(p_1-p_2)^2]$$

Where:

$n_t$  = sample size

$z_{\alpha/2}$  = the corresponding value to the 95% CI

$z_{\beta}$  = The corresponding value to power of 90%

$p_1$  = anticipated cure rate = 95%

$p_2$  = worst case scenario = 85%

$q_1 = 1 - p_1$

$q_2 = 1 - p_2$

where  $k = 10.5$  for power of 90%

For 90%

$$n_t \geq 10.5 [(0.85(0.15) + 0.95(0.05))/0.01] = 184$$

The sample size was adjusted to account for attrition rate due to loss to follow up, which is anticipated to be 15%. Thus the minimum sample size becomes  $n = 217$ .

HIV/AIDS was likely to be a covariate that could affect the primary variable-cure rate, especially in Ethiopia where the co-infection rate is estimated to be above 20%. This necessitated a further adjustment of the sample size for Ethiopia by 20% in order to be able to attribute the true treatment effect of the test drugs after controlling for HIV/AIDS. Thus the total for the three arms is 695.

The participating teams from Kenya, Ethiopia, Sudan and MSF were asked to specify the number of cases they could conveniently handle given the existing capacity and available infrastructure. This approach was used in absence of any other criteria. On the other hand some of the countries have very high case-load.

Table 1: Sample size per group

| Teams                      | Expected Sample per Group(rounded to complete block of 15) |
|----------------------------|------------------------------------------------------------|
| Kenya                      | 60                                                         |
| Sudan MSF                  | 150                                                        |
| Sudan MOH                  | 225                                                        |
| Ethiopia – Gondar Province | 150                                                        |
| Ethiopia-Southern Province | 120                                                        |
| Total                      | 705                                                        |

For further reading on sample size estimation consult (Chan 2003)

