## **HYPOTHESIS**

That a combination course of SSG and PM (17 days) is similar in efficacy to either PM alone(21 days) or SSG alone (30 days) and that the shorter course combination (17 days) is not more toxic than PM or SSG alone.

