#### **Analysis**

In the analytical approach intention to treat will be used. The aim is to estimate the difference in treatment outcomes for the three arms. The intention to treat analytical method will take care of events such as patient withdrawal from the trial, failure to comply with treatment, change in treatment and lost to follow-up.

There are two basic options:

Analyse final outcome only for those who complied perfectly with each treatment

Analyse data for all subjects in the groups to which they were randomized. This is referred to as 'Intention to treat' analysis or the 'pragmatic approach'.

The second option will be adopted, analysis will be carried out according to the original treatment assignment regardless of adherence to treatment or protocol.

There will be no exclusion of patients or events. Drop-outs will be checked to establish whether they were systematic or non-random. The analysis will, as much as possible stick to the protocol to avoid data dredging as part of post ad hoc analysis.

Note: Specific country analysis will be of little value because it lacks power. The data will have to be pooled for it to achieve the necessary power in the efficacy analysis.

Summary statistical measures to be computed

The summary statistics will include the  $\chi^2$  and risk ratios per arm for the overall efficacy comparison. The analysis and interpretation will heavily rely on confidence intervals of the cure rates among the three arms of the RCT. Other estimations to be made will be the calculation of the power finally achieved by the trial. This will be followed by the presentation of the results in terms of basic descriptive statistics and statistical diagrams. Finally multivariate analysis will be carried out to establish the socio-demographic factors associated with the main parameters.

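### The hypotheses aim to show that the arms do not differ, but the 90% power is for detecting a 95% v 85% difference and no margin is stated

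*Protocol*

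**What the plan says.** - **Protocol, HYPOTHESIS:** the combination "is similar in efficacy to either PM alone(21 days) or SSG alone (30 days" courses.
- **Protocol, Sample size Determination, hypotheses:** the hypothesis to be tested is that "The three therapies differ by clinically relevant amounts", and the alternative is that "The three therapies do not differ by clinically relevant amounts". This is the layout of an equivalence-type problem: lack of a relevant difference is what has to be shown.
- **Same section, sizing:** cure rates of 95% (anticipated) and 85% (worst case) are entered in a two-proportion formula. Of these the text says: "The difference of these two proportions gives the size of the treatment effect sought in the randomized clinical trials". It also says: "A power of 90% and 5% level of significance are also required". The z value for alpha is "the corresponding value to the 95% CI", so the calculation is two-sided. The result is 184 per arm, raised to 217 for 15% attrition and to 695 in total after an HIV adjustment for Ethiopia. The table of teams rounds this to 705.
- **Protocol, Analysis:** all patients are analysed as randomised. The measures named are chi-square and "risk ratios per arm for the overall efficacy comparison". Interpretation is to rest heavily on confidence intervals of the cure rates. A further item is the "calculation of the power finally achieved by the trial".
- **Protocol, Criteria for Patient Withdrawal:** withdrawn patients are analysed as having failed to respond, and loss to follow-up is listed among the reasons for withdrawal.

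**The concern.** The hypotheses, the sample size and the named test do not answer the same question. The hypotheses ask whether the arms can be shown not to differ by a relevant amount. The formula and the chi-square ask whether they can be shown to differ. Power belongs to the alternative: it is the chance of reaching that conclusion when it is true. Here the 90% is computed at 95% v 85%, a gap that the section treats as the effect worth finding and that therefore sits in the protocol's own null.

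What is at stake is the primary conclusion. No margin is given and no rule says when the arms count as not differing, so nothing in the protocol fixes what result would support the stated alternative. A margin first chosen later, in an open-label trial, would be open to challenge. The achieved-power calculation does not fill the gap: computed from the observed effect, it only re-expresses the p-value.

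**Working it through.** **1. Reproduce the plan's figure.** Inputs from Sample size Determination: p1 = 0.95, p2 = 0.85, k = 10.5, which is (1.960 + 1.282)².

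n = 10.5 × (0.85×0.15 + 0.95×0.05) / 0.10² = 10.5 × 0.175 / 0.01 = 183.75, so 184 per arm.

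184 / 0.85 = 216.5, so 217. Then 3 × 217 + 0.20 × 217 = 694.4, so 695. The arithmetic is right. The planned 705 gives 705 / 3 = 235 per arm.

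**2. What the 90% is.** At 184 per arm and 95% v 85%, SE = √(0.175/184) = 0.0308. Power = Φ(0.10/0.0308 − 1.96) = Φ(1.28) = 90%. This is the probability of a significant difference when a 10-point difference exists.

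**3. Can a non-significant chi-square support the alternative?** P(non-significant) = 1 − Φ((|p1−p2| − 1.96·SE0)/SE1), with SE0 pooled and SE1 unpooled, at 184 per arm:

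| True rates | SE0 | SE1 | P(non-significant) |
|---|---|---|---|
| 95% v 90% | 0.0275 | 0.0273 | 56% |
| 90% v 85% | 0.0345 | 0.0344 | 70% |

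At 235 per arm the same formula gives 46% and 63%. Non-significance is a common result when a 5-point gap exists, so it does not establish similarity.

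**4. Power for the stated alternative.** This needs a margin and equal true rates. The protocol names no margin; 10 points is an assumption borrowed from its own effect size. For one pair, with 235 per arm and a 95% confidence interval:

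SE = √(2p(1−p)/235); non-inferiority power = Φ(0.10/SE − 1.96); equivalence power (interval within ±10 points) = 2Φ(0.10/SE − 1.96) − 1.

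| Common cure rate | SE | 0.10/SE − 1.96 | Non-inferiority | Equivalence |
|---|---|---|---|---|
| 95% | 0.0201 | 3.01 | 99.9% | 99.7% |
| 90% | 0.0277 | 1.65 | 95% | 90% |
| 85% | 0.0329 | 1.08 | 86% | 72% |
| 80.75% | 0.0364 | 0.79 | 79% | 57% |

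The last row is 0.95 × 0.85 = 0.8075: a true 95% if the full 15% expected loss is counted as failure. That is an assumption about how the withdrawal rule would act.

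**5. Both comparisons in HYPOTHESIS.** If the combination must succeed against SSG and against PM, simulation at 235 per arm (200,000 trials, same margin) gives non-inferiority power of 99.7%, 92% and 78%, and equivalence power of 99%, 83% and 55%, at 95%, 90% and 85%.

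**6. Sensitivity to the margin.** With a 5-point margin, one-pair equivalence at 90% power would need 494, 936 and 1326 per arm at common rates of 95%, 90% and 85%. The missing margin therefore decides whether the planned size is ample or far too small.

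**The case against.** The strongest reply has four parts.

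- **The protocol never says that a non-significant chi-square means similar.** This stands. A reader might infer that rule from the hypotheses and the named test, but no section states it. The Analysis section gives estimating the difference as its aim and leans on confidence intervals. Intervals could serve an equivalence conclusion, but those described are of the cure rates in the arms, and no limit on a between-arm difference is set.
- **The size may be adequate anyway.** This largely stands. A reader might infer that the trial is underpowered. At the anticipated 95% cure, with a 10-point margin, power for similarity is above the stated 90%; the shortfalls come at lower cure rates or with a tighter margin.
- **It would be unfair to say that the true power is 2.5% rather than 90%.** This stands. At 95% v 85%, 2.5% is only the type I error at an assumed 10-point boundary, and the protocol does not claim 90% power to conclude equivalence there. At that same gap, chi-square at 184 per arm is non-significant only about 10% of the time. The examples in step 3 are 5-point gaps, and whether 5 points is relevant depends on the margin that is missing.
- **The statistical analysis plan may settle it.** This does not stand. The hypotheses, the power basis and the named test are fixed in the protocol and conflict there.

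Nor does the two-directional wording mean that any advantage of the combination would defeat the hypothesis; only an advantage of a clinically relevant size would. The achieved-power item is listed among other estimations, not as a decision criterion, so it is a minor part of this point.

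**Conclusion.** The contradiction is real and lies within the protocol. The stated 90% is correct arithmetic for detecting 95% v 85%, and it is not power for the stated alternative. No margin or decision rule says what result would support that alternative.

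The size of the problem depends on the margin and the cure rate. With an assumed 10-point margin, equal true rates and 235 per arm, one-pair power runs from 99.9% to 86% for non-inferiority and from 99.7% to 72% for equivalence, over cure rates of 95% to 85%. It falls to about 79% and 57% if the expected 15% loss all counts as failure. The documents support neither a finding of general underpowering nor a claim that non-significance is to be read as similarity.

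**What to change.** Reconcile HYPOTHESIS, Sample size Determination and Analysis in one of two ways.

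1. **Test of difference.** Restate the hypotheses so that equality is the null. The 184 per arm and the chi-square are then valid as they stand, and similarity is dropped as a conclusion.
2. **Keep the aim of showing no relevant difference.**
   - State a clinically justified margin; the 10 points used above is only an assumption taken from the sample size section.
   - State whether the claim is equivalence or non-inferiority.
   - Name both comparisons in HYPOTHESIS: combination v SSG and combination v PM.
   - Base the conclusion on the 95% confidence interval of the cure-rate difference, with chi-square supportive.
   - Restate the power under equal cure rates for the all-randomised analysis with withdrawals as failures. Power figures at 184 evaluable per arm should not be used for this, because they do not match that analysis.

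Under either choice, do not use the achieved-power calculation to interpret the result.

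The cost is wording only. Under the second choice the stated power may become less favourable at lower cure rates, and a margin tighter than 10 points could reopen the sample size.

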### **Need for new treatment options**

In eastern Africa, the first line treatment today in most endemic areas is antimonial therapy for 4 weeks sodium stibogluconate, (Pentostam® from GSK in Kenya or generic SSG from Albert David in Sudan and Ethiopia) used at 20 mg/kg/day for 28-30 days). Although the efficacy of this treatment is not yet compromised by resistance in this region (in contrast to Bihar – India), the painful daily injections, the need for four weeks of hospitalisation, the toxicity when using longer treatments, the low efficacy in HIV co-infected patients and the risk of inevitable drug resistance, as observed in India, make alternative options a necessity. Second line treatments are either toxic or prohibitively expensive.

In 2002-3, a combination of SSG and PM given for 17 days was used in an epidemic situation in Southern Sudan, with an initial cure rate of 97% (personal communication from [name], Médecins Sans Frontières). These findings were in line with previous published experience in the same area (Seaman et al, 1993) and experience in Kenya (Chunge et al, 1990). The proposed study aims to confirm these results in a randomized prospective comparative study.

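### The 5% level and 90% power are computed for a 95% v 85% difference in one unnamed pair of arms, so the 90% is not established for the two- and three-arm similarity claims it is attached to

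*Protocol*

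**What the plan says.** In the protocol's Sample size Determination section, the hypothesis to be rejected is that the three therapies differ by clinically relevant amounts; the alternative is that they do not. The section then says "A power of 90% and 5% level of significance are also required". Its formula contains two cure rates only, 95% (anticipated) and 85% (worst case), with k = 10.5. It gives 184 per arm, raised to 217 for 15% attrition. The total for three arms becomes 695 after an HIV adjustment for Ethiopia, and 705 after rounding to blocks.

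Other sections frame the question differently:

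- **Hypothesis:** the combination is "similar in efficacy to either PM alone(21 days) or SSG alone (30 days"), which is two comparisons.
- **Objectives of the Trial:** the efficacy and safety of each regimen are to be assessed separately; no comparison is named.
- **Analysis:** a chi-square and risk ratios are planned for the overall efficacy comparison, and "The analysis and interpretation will heavily rely on confidence intervals of the cure rates among the three arms of the RCT". No primary contrast, order of testing or decision rule is given.
- **Need for new treatment options:** after reporting earlier results with the 17-day combination, it says "The proposed study aims to confirm these results in a randomized prospective comparative study".

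**The concern.** Significance level and power belong to a particular test of a particular claim. Here they were calculated for finding a difference in one pair, and are quoted for concluding that two or three pairs do not differ. Showing several pairs similar at once generally has a different power from detecting one difference, and that power depends on a margin and on the true cure rate.

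More than one claim may follow from the trial. Trial Objectives and Purpose looks to introducing the combination if it is proven efficacious and safe, and Ethical Considerations looks to registering paromomycin if it is found efficacious and safe. In an open-label trial with no named primary pair, the contrast that carries the conclusion could be settled after the results are known, and a reader could not tell which claim had 90% power.

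**Working it through.** **Inputs (Sample size Determination).** p1 = 0.95, p2 = 0.85, equal allocation, 90% power, two-sided 5%. The z-value is described as "the corresponding value to the 95% CI", and (1.960 + 1.282)² = 10.51 agrees with k = 10.5.

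**1. The plan's own figure.** n = 10.5 × (0.85 × 0.15 + 0.95 × 0.05) / 0.10² = 10.5 × 0.175 / 0.01 = 183.75, so 184. Attrition: 184 / 0.85 = 216.5, so 217. Both reproduce. They are two-arm figures, and the same n is then used for each of three arms.

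**2. Power for 95% v 85% in one pair.** Power = Φ(0.10 / √(0.175/n) − z). The first term is 3.243 at n = 184. It is 3.381 at n = 200, roughly what remains of 705/3 = 235 after 15% loss (235 × 0.85 = 199.75).

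| Two-sided level | z | n = 184 | n = 200 |
|---|---|---|---|
| 0.05 | 1.960 | 90% | 92% |
| 0.05/2 | 2.241 | 84% | 87% |
| 0.05/3 | 2.394 | 80% | 84% |

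**3. Type I error, by decision rule, when all arms have the same cure rate.**

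- Three unadjusted pairwise 5% tests, each able to support a claim: 1 − P(range of three standard normals ≤ 1.96√2) = 12.2%.
- Two unadjusted tests sharing one arm (correlation 0.5): about 9%.
- Overall chi-square on 2 degrees of freedom at 5%: about 5% by simulation at 184 per arm.

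For a rule that concludes similarity only if every pair is shown similar, the relevant error is a false claim of similarity. Requiring all pairs to pass does not inflate it.

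**4. Power of the overall chi-square at 184 per arm (simulated).** 93% for true rates 95/85/85, 94% for 85/95/95 and 84% for 95/90/85.

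**5. Power for the similarity claims at 184 per arm.** Two assumptions are needed because the protocol gives neither a margin nor a rule: a margin of 10 points (the gap between 95% and 85%), and similarity declared when the 95% confidence interval for the difference lies wholly within ±10 points. For one pair, the normal approximation is 2Φ(0.10 / √(2p(1−p)/184) − 1.96) − 1. At p = 0.90 the standard error is 0.0313 and the power 78%. Simulated results with the three true rates equal:

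| True cure rate | One pair | Two pairs (combination v each single agent) | All three pairs |
|---|---|---|---|
| 95% | 98% | 96% | 95% |
| 90% | 78% | 64% | 57% |
| 85% | 54% | 32% | 27% |

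**The case against.** The strongest reply is that the Analysis section does name an overall chi-square. With that test the type I error stays at about 5%, and power is 93–94% when one arm differs from the other two by 10 points. So both stated figures hold approximately for one natural three-arm question at the protocol's own effect size. This stands. It answers whether a difference can be detected, however; a non-significant chi-square does not show that the therapies are similar, which is the claim in the Hypothesis section and the written alternative in the sample size section.

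A reader might infer that the trial's false-positive rate is 12%. The documents do not support that. The figure needs a rule under which each unadjusted pair carries its own claim, and the protocol states no such rule. A reader might also infer that the trial is underpowered for similarity. That does not follow either: at the anticipated 95% cure rate, 184 per arm gives about 95% for all three pairs under the assumed margin. The low figures belong to the lower part of the protocol's own 85–95% range.

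Three further points are fair:

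- Planned enrolment exceeds the bare calculation, so with about 200 evaluable per arm the adjusted powers are 87% and 84%, not 84% and 80%.
- The Analysis section undertakes to keep to the protocol and avoid data dredging. That helps little while the protocol names no comparison to keep to.
- Testing order and multiplicity adjustment are commonly left to a statistical analysis plan, which is not at hand, so their absence is not the fault here. The fault is that the sample size section ties its figures to a claim for which they were not computed, and a later plan cannot alter what 184 was calculated for.

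**Conclusion.** The point holds in limited form. The arithmetic is right; what is wrong is the claim to which its result is attached. The 90% describes detection of a 95% v 85% difference in one pair at an unadjusted two-sided 5%. It is not established for similarity of the combination to both single agents, or of all three therapies.

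How far the true power lies from 90% depends on the margin and the cure rate. With a 10-point margin, which is an assumption, it ranges from 96% down to 32% for two pairs and from 95% down to 27% for three pairs as the true cure rate falls from 95% to 85%. The 5% level is at risk only under unadjusted pairwise claims. The documents therefore do not support saying that the stated error rate and power fail outright; they support saying that the protocol does not fix which contrast or rule the two figures describe.

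**What to change.** In Sample size Determination:

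1. Name one primary comparison in advance. Combination v SSG is consistent with Need for new treatment options and with Trial Objectives and Purpose, since the combination is what the trial sets out to confirm and SSG is the current first-line treatment.
2. Place the remaining comparisons in a fixed order, or report them as estimates with confidence intervals. If the sponsor prefers to require similarity to both single agents together, say so; that rule needs no adjustment of the level, but its joint power must be given.
3. State that the 5% and 90% refer to a single pairwise 95% v 85% difference.
4. Restate the power for the similarity claim actually made, with its margin and assumed cure rate. The 90% must not be carried over even to one named pair: under the assumptions above, single-pair power for similarity is 98%, 78% or 54% at true cure rates of 95%, 90% or 85%.

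Bring the Hypothesis and Analysis sections into line with the choice.

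The cost is wording plus the choice and justification of a margin, with no extra patients. The downsides are that the other comparisons become secondary, including combination v PM, which the Hypothesis section now places on an equal footing, and that the restated power may be below 90%.

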### **CRITERIA FOR PATIENT WITHDRAWAL**

Patients will be considered to have completed the study if they satisfy all entry criteria, complete the course of treatment and attend the 6 month follow-up visit.

Patients will be considered to have withdrawn from the study if they had entered into the study (i.e. gave informed consent and received at least one day's treatment) but did not complete the treatment period and follow up period.

Treatment failure will be defined as no change or an increase in the patient's disease severity i.e. in signs and symptoms of VL, and parasitology, such that the patient is withdrawn from the study and alternative therapy given.

A patient may be withdrawn from the study at any stage if the investigator or the DSMB considers there is a serious risk to the patient from continuation in the protocol. Alternative therapy will be provided to the patient if needed, upon withdrawal from the study.

A patient may withdraw, or be withdrawn, from the study for one of the following reasons:

- Serious adverse events (drug related or not)
- Deviation from protocol (including non-compliance)
- Lost to follow-up
- Termination by the sponsor
- Withdrawal of consent

The reason for termination will be recorded on the CRF. Patients withdrawn from the study will be followed-up at 3 and 6 months for monitoring of adverse events wherever possible. Every effort will be made to follow up withdrawn patients in order to determine the final outcome. This information will be recorded in the CRF and these patients data will be analysed as those who failed to respond to treatment.

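### The sample size treats the expected 15% lost to follow-up as excluded, but the protocol analyses them as failures; on the protocol's own inputs power is about 55–59%, not 90%

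*Protocol*

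**What the plan says.** **Sample size (Protocol, Sample size Determination).** "A cure rate of 85% to 95% was used in the sample size calculation", and "A power of 90% and 5% level of significance are also required". The normal quantile for the significance level is described as "the corresponding value to the 95% CI", so the test is two-sided. Allocation is "uniform and equal allocation where" the ratio is 1. The result is 184 per arm. The section continues: "The sample size was adjusted to account for attrition rate due to loss to follow up, which is anticipated to be 15" per cent, giving 217 per arm. After a further 20% adjustment for HIV in Ethiopia, "Thus the total for the three arms is 695"; the table that follows rounds to complete blocks and totals 705, or 235 per arm.

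**Handling of lost patients (Protocol, Criteria for Patient Withdrawal).** A patient completes the study only by attending the six-month visit. Loss to follow-up is one of the listed reasons for withdrawal. The section ends by saying of withdrawn patients that "these patients data will be analysed as those who failed to respond to treatment".

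**Analysis set (Protocol, Analysis).** Intention to treat is adopted, loss to follow-up is named among the events it is meant to deal with, and "There will be no exclusion of patients or events".

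**The concern.** Dividing by 0.85 restores the number of evaluable patients to 184. That protects power only if the lost 15% are absent from the analysis and the rest still show 95% and 85%. The withdrawal criteria instead keep the lost patients in the denominator as failures, in every arm. This lowers each cure rate, narrows the difference between arms, and moves both rates towards the middle of the scale, where the binomial variance is larger. The planning rates were not lowered to match.

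Two things are at stake. The 90% power for the primary comparison does not exist under the stated analysis rule. And because the trial's hypothesis is that the combination is similar to the single drugs, adding the same share of failures to every arm makes a truly inferior arm look closer to its comparator than it is.

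**Working it through.** **Inputs, all from Sample size Determination unless noted.** Cure rates 0.95 and 0.85; two-sided 5%; power 90%; k = 10.5; equal arms; 15% loss; 217 per arm after inflation; 705 in total after block rounding, so 705/3 = 235 per arm. The failure rule comes from Criteria for Patient Withdrawal.

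**1. Reproduce the plan's figures.**
- n = 10.5 × (0.85×0.15 + 0.95×0.05) / 0.10² = 10.5 × 0.175 / 0.01 = 183.75, rounded up to 184.
- 184 / 0.85 = 216.5, rounded up to 217.
- 3 × 217 + 0.20 × 217 = 694.4, consistent with the stated 695.

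If lost patients are excluded, 217 × 0.85 = 184.45 evaluable patients give 90.1% power, and 235 × 0.85 = 199.75 give 92.2%. The plan is coherent under exclusion.

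**2. Can 95% already be net of loss?** No. With 15% counted as failures, no arm can exceed 85% cure. The 95% and 85% must be rates among followed patients.

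**3. Rates under the protocol's failure rule.**
- 0.85 × 0.95 = 0.8075 and 0.85 × 0.85 = 0.7225; difference 0.085.
- Summed variance: 0.8075×0.1925 + 0.7225×0.2775 = 0.3559, against 0.175 in the plan.

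**4. Power**, from the same unpooled formula: Φ(0.085 / √(0.3559/n) − 1.96).
- n = 217: 0.085/0.0405 − 1.96 = 0.139, so 55.5%.
- n = 235: 0.085/0.0389 − 1.96 = 0.224, so 58.9%.

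A pooled-variance test gives 55.1% and 58.5%; simulation gives 55.3% and 58.9%.

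**5. Sensitivity to the loss rate** (lost counted as failures, unpooled formula):

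| Loss in each arm | 217 per arm | 235 per arm |
|---|---|---|
| 5% | 81.0% | 83.9% |
| 10% | 67.2% | 70.7% |
| 15% | 55.5% | 58.9% |

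**6. Size needed for 90% under the failure rule.** 10.5 × 0.3559 / 0.085² = 517.3, so 518 per arm (521 with the pooled formula).

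**7. If the aim is read as similarity.** The protocol sets no margin. Assume 10 points with a one-sided 2.5% non-inferiority test. Compare 184 evaluable patients (lost excluded) with 217 randomised (15% lost, scored as failures):
- Both true rates 95%: power falls from 99.3% to 75.2%.
- Both true rates 85%: power falls from 76.6% to 64.3%.
- True 10-point deficit (95% v 85%), 235 per arm: the chance of wrongly accepting non-inferiority is Φ((0.10 − 0.085)/0.0389 − 1.96) = 5.8%, instead of 2.5%.

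**The case against.** **The 55–59% is conditional.** It needs 15% loss in each arm, and that figure is a planning allowance, not an observation. The Indian studies tabulated under Dose finding Studies show 7 defaulters among 390 enrolled (1.8%); at that rate the same formula gives about 92% at 235 per arm. This stands as a caution on how large the shortfall would turn out to be. It does not rescue the plan, which chose 15% and must be coherent at 15%.

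**The hypothesis is similarity, so power to detect a difference is beside the point.** The wording of the hypotheses does point that way, but the protocol's formula is the one for a difference, and its 90% belongs to that test. Under an assumed 10-point margin the loss of power is smaller but remains, and a false-acceptance problem is added.

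**The failure rule may not be meant for patients with no outcome.** The withdrawal section promises efforts to establish final outcomes, and the Analysis section will check whether drop-out is systematic, which would matter little if every lost patient were simply a failure. Nor does the Analysis section itself say that missing means failure. The statistical analysis plan, not at hand, might say more. Even so, the withdrawal section still scores these patients as failures after the promised follow-up, and both the size and the rule are fixed in the protocol. Reading the rule more narrowly would leave no stated outcome for patients who may not be excluded, which does not match the inflation either.

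**No sum is wrong.** True: 184 and 217 are exact. The fault is a mismatch between the size calculation and the analysis rule.

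**Conclusion.** The concern holds. The inflation to 217 and the rule that lost patients are failures cannot both stand with 90% power. On the protocol's own rates, loss and formula, power is 55.5% at 217 per arm and 58.9% at the planned 235, a shortfall of more than 30 percentage points. Neither the HIV increment nor block rounding cures it, since the 235 already includes both.

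The figure assumes 15% loss in each arm, loss unrelated to outcome, every lost patient scored a failure, and pairwise two-sided 5% tests without multiplicity adjustment. The inconsistency itself needs none of these, because a planned 95% cure rate is unattainable once 15% are failures by definition. The 5.8% false-acceptance figure rests additionally on a 10-point margin that the protocol does not set.

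**What to change.** Align Sample size Determination with Criteria for Patient Withdrawal and Analysis, by one of these routes:

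- **(a) Change the analysis rule.** Base the primary analysis on observed six-month outcomes, with multiple imputation for patients lost to follow-up, and keep lost-as-failure as a sensitivity analysis. The 217 is then coherent. Imputation assumes that loss is explained by the observed data; the planned check of drop-outs bears on this and should be reported with the result. Cost: wording.
- **(b) Keep lost-as-failure and restate the calculation.** Give the planning rates as 80.75% and 72.25% and the power as about 59% at 235 per arm. Cost: wording and a less favourable stated power. This makes the plan honest but restores neither the power nor the protection against a false finding of similarity.
- **(c) Keep lost-as-failure and the 90%.** This needs about 518 per arm, or 3 × 518 = 1,554 in total against 705, and the dilution of a true difference would remain.

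Routes (a) and (b) need no extra patients. Under any route, state the loss rate assumed and show power over a range, for example 5% to 15%.
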